## Abstract

**Background:**

Culturally competent parent training in evidence-based intervention for autism spectrum disorder (ASD) can provide young Latinx children from underserved communities with early interventional support while they wait for professional services, thus reducing the impact of intervention delays. Providing parents with brief bilingual training in Pivotal Response Treatment (PRT) is a strategy that can overcome these barriers and is inexpensive to disseminate. Brief PRT training has been shown to significantly improve joint attention, expressive language, responsivity, and adaptive skills in young children with ASD. However, it is unknown whether an interactive, culturally competent online parent training in PRT is effective in a Latinx population.

**Objective:**

To this end, we will recruit 24 children (16-36 months old) at risk for ASD and their parent(s) from East and South Los Angeles and provide them with a series of 6 online learning modules in their choice of Spanish or English.

**Methods:**

This pilot study will utilize a single-group, pilot, pre-post design with follow-up assessments 6 weeks later. Linear mixed-effects model analysis will be used to explore most parent-reported and coded outcomes.

**Results:**

Brief online parent training in evidence-based treatments has the capacity to increase access to culturally competent early communication interventions for young children at risk for ASD.

**Conclusions:**

The results of this trial may have particular salience in additional underresourced communities where children have limited access to interventions prior to entering school.

**International Registered Report Identifier (IRRID):**

PRR1-10.2196/18004

## Introduction

### Background

Early access to evidence-based intervention leads to best-case, long-term outcomes for children with autism spectrum disorder (ASD) [1], with the greatest developmental gains experienced by children who begin intervention before their third birthday [2,3]. A recently published meta-analysis revealed that intervention benefits to social communication begin to diminish before a child turns 4 years, highlighting the importance of ASD-focused early intervention services in the developmental period [4]. Delay in the receipt of ASD-focused intervention has been associated with later autism severity, placement in segregated learning environments, and lower scores on tests of student achievement [5].

Parents from underserved communities often have less knowledge about ASD and are less likely to recognize ASD symptoms [6,7]. Therefore, their children are less likely to receive an early diagnosis of ASD. This marks a missed opportunity for intervention during the critical developmental period. Additionally, underserved families may find interventions that require a significant time commitment or cause their child to react emotionally untenable due to cultural mismatch [8].

Targeted outreach to early childhood centers and coordination with early intervention systems and health care providers, paired with dissemination of culturally competent, parent-mediated intervention models are crucial to reduce this service-need discrepancy for underserved families [9]. White, middle to upper class participants represent a significant majority in quality research studies of evidence-based practice for young children with ASD, so it is yet unclear whether established treatments are effective in nonprivileged or racially or ethnically diverse samples [10]. Virtual parent training interventions for ASD that have shown merit utilize telehealth models [11,12] that are limited by inflexible scheduling, as parents must be available to attend at predetermined times, require hard-copy hand-outs, and are limited to English-proficient participants. To make parent-mediated interventions more accessible to diverse samples of families, it has been suggested that clinicians make training materials less complicated, allow for flexibility in how the program is delivered, and teach families how to practice the intervention within their preexisting routines [13,14].

### Research With Latinx Families of Children With ASD

According to recent qualitative research on the implementation of evidence-based interventions for ASD in Latinx families, parents frequently have limited knowledge regarding ASD and require additional information. However, they are ultimately eager to participate in teaching their child and focused on helping them improve their functioning [15]. Latinx mothers of young children with ASD may also have a heightened sense of guilt regarding their child’s diagnosis, possibly believing it a punishment for something they have done in the past [16], making the delivery of accurate, culturally informed Spanish language information and intervention even more crucial [17]. In addition to these barriers, the climate of anti-immigrant sentiment and media coverage of the Immigration and Customs Enforcement detention centers and family separations may keep Latinx families who need services for their young children from seeking help.

Providing Latinx parents with brief online training in Pivotal Response Treatment (PRT) strategies in their language of preference can help overcome barriers and reduce disparities. Brief PRT training has been shown to significantly improve joint attention, expressive language, responsivity, and adaptive skills in young children with ASD [18,19]. And a recently published report on a pilot study of an online PRT parent training reported significant improvements in parent fidelity of implementation and social communication in a diverse sample of young children [20]. However, brief online PRT training has not been tested for effectiveness in a bilingual Latinx sample.

Latinx families have rapidly grown to be among the highest users of smartphone technology [21], and recent eHealth studies have shown preliminary success in using mobile technology to increase knowledge regarding diagnosis and improve health-related behaviors [22]. To this end, we are in the process of developing a smartphone-optimized, interactive, bilingual, culturally competent brief online PRT training curriculum titled “Helping Optimize Language Acquisition” (HOLA) with feedback from an advisory committee comprised of a bilingual parent of a young child with ASD, a PRT expert with over 20 years of experience in parent-mediated PRT coaching, and a bilingual Early Intervention (EI) program administrator. The HOLA curriculum is based on the information, lessons, and examples included in “Using Pivotal Response Treatment to Teach First Words to Children with Autism” [23] and “Pivotal Response Treatment: Using Motivation as a Pivotal Response” [24] by Koegel, as well as information from “Parents Taking Action,” a culturally informed bilingual training program for parents of children with ASD or developmental disabilities [25]. HOLA will be delivered to parents in 6 brief (20-40 minute) weekly modules in English or Spanish (Textbox 1).

Topics addressed in each of the 6 modules in the Helping Optimize Language Acquisition (HOLA) program.Module 1Child DevelopmentAutism Spectrum DisorderModule 2Child ChoiceGetting StartedNatural EnvironmentsFavorite Things!What is HOLA?Module 3Providing Natural RewardsWhat are Natural Rewards?Rewarding Good TryingEasy TasksModule 4Providing Clear OpportunitiesGetting Your Child’s AttentionProviding a Clear OpportunityResponding Right AwayModule 5Putting it All TogetherReviewing the StrategiesTeaching in Daily RoutinesCelebrating Your ChildModule 6Planning for the FutureTroubleshootingTask VarietyFamily BalanceTaking Care of Yourself

The HOLA modules will differ from other virtual parent trainings in that they will be accessible online at any time of day, they can be viewed multiple times, and all needed materials will be integrated into the training modules. The HOLA training will make use of adult learning principles and use multiple modalities including presentations, visual representations, gamification, and video examples to teach the content, and text will be simplified and supported by visuals to allow for participants of varying levels of literacy (Figures 1 and 2). These training strategies have been shown to improve learning outcomes when compared to traditional presentation methods such as narrative slideshows for a variety of learners [26].

**Figure 1 figure1:**
[figure not shown]
Example video enhanced page from an HOLA module.

**Figure 2 figure2:**
[figure not shown]
Example interactive page from an HOLA module.

## Methods

### Objectives and Study Design

This pilot study will utilize a single-group, pilot, pre-post design with follow-up assessments 6 weeks later. All assessments described in the subsequent paragraphs are available in English and Spanish. It is hypothesized that the HOLA parent training will improve parent knowledge of ASD and child development, increase fidelity of implementation of the strategies taught, and improve child social communication. Additionally, we predict that the parent will experience gains in empowerment and reductions in parenting stress, and the children will have reductions in challenging behavior and display improved social skills. Finally, we predict that there will be no difference in participant outcomes between Spanish and English language trainings.

To test the HOLA intervention, we will recruit 24 Latinx toddler-parent dyads (16-36 months old) with elevated risk for ASD from the East and South Los Angeles regions to measure the effects of the HOLA intervention on parent knowledge of child development, parent PRT fidelity of implementation, and child social communication. We will also measure parent satisfaction with the intervention and explore the impact of HOLA on parent stress, family empowerment, and child behavior. Additionally, because participants will choose whether they would prefer to receive the intervention in Spanish or English, we will assess whether language has an impact on effectiveness of and satisfaction with HOLA.

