### Sample Size Determination

A recently published report on a monolingual, brief, online, PRT pilot reported significant improvement in parent fidelity of implementation of PRT strategies and measures of child social communication (vocalizations, eye contact, and positive affect) after 5 weeks, with large effect sizes of 1.80 and 1.12, respectively [20], similar to findings from earlier studies. Therefore, given a conservative estimated effect size of 0.8 for our primary outcomes between baseline and postintervention timepoints, a sample size of 13 is needed to have 80% power to detect a significant difference in primary outcomes between these timepoints given an α of .05. Given our goal of enrolling 24 participant dyads and assuming normal distributions, we can estimate 97% power to detect a significant difference in primary outcomes between baseline and postintervention.

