### Quantitative Analysis

Linear mixed-effects model analysis will be used to explore most parent-reported and coded outcomes because (1) it allows for individual differences in parent responses over time to be included in the model as a random effect so that the variance in responses is partitioned into a time-within-parent component and a between-parent component, (2) using maximum likelihood estimation in a linear mixed-effects model allows for the use of all available data to evaluate the parameter values and is currently considered the state-of-the-art method for handling missing data, and (3) linear mixed-effects models perform well with small samples. The linear mixed-effects models will evaluate time as the main fixed effect using discrete time variables (ie, 2 dummy variables with baseline as the “referent”). Separate regression models will be run for each outcome. Additional variables to be included in each regression model will include total score of other services used, recruitment site, and only demographic variables significantly related to the outcome (given the small sample size).

Cohen d effect sizes will be calculated between time periods and reported for all analyses of interest as a measure of the magnitude of any changes in outcome measures. Mixed models will also be utilized to test if changes from baseline on outcome variables differ by parent language preference for training (Spanish or English) over time. HOLA acceptability will be determined by the average parent rating on the Parent Satisfaction measure. If the average ratings for parent satisfaction items are 3.5 or higher, the training may remain as written. Items with parent satisfaction ratings lower than 3.5 will be explored during Spanish and English focus groups, and individual items will be refined according to feedback. Focus group transcripts will be coded and analyzed thematically to inform continued program improvement.

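### The plan predicts no difference between Spanish and English training, but the only analysis it gives for change in outcomes is a difference test, which cannot support that prediction with 24 dyads

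*Protocol article*

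**What the plan says.** The Objectives and Study Design section of the protocol article ends its list of hypotheses with a prediction about language: "we predict that there will be no difference in participant outcomes between Spanish and English language trainings". The next paragraph gives the sample, "we will recruit 24 Latinx toddler-parent dyads (16-36 months old) with elevated risk for ASD", and explains that "participants will choose whether they would prefer to receive the intervention in Spanish or English". It adds that the study will look at whether language affects the effectiveness of the training and satisfaction with it.

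For change in outcomes, the Quantitative Analysis section gives one method: "Mixed models will also be utilized to test if changes from baseline on outcome variables differ by parent language preference for training". It also says that each outcome model will include "total score of other services used, recruitment site, and only demographic variables significantly related to the outcome".

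The Sample Size Determination section concerns only the change from baseline to postintervention in the whole sample. It states that "a sample size of 13 is needed to have 80% power to detect a significant difference in primary outcomes between these timepoints", "given a conservative estimated effect size of 0.8 for our primary outcomes between baseline and postintervention timepoints", and that with 24 dyads "we can estimate 97% power to detect a significant difference in primary outcomes between baseline and postintervention". It claims no power for the language comparison.

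The article gives no equivalence margin and no confidence-interval criterion for language. It does not say how a non-significant language result will be interpreted.

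**The concern.** The prediction is itself a null hypothesis, and the analysis named for it is a test of that null. A significant language-by-time term would contradict the prediction. A non-significant term would leave it open, because non-significance is also the common result when a real difference exists and the sample is small. Hypothesis and test are both stated in the article and do not fit each other, so this is not a detail left to an analysis plan.

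Delivery in two languages is a distinguishing feature of the programme. If a non-significant result were taken as showing that the two versions work equally well, a version that works less well for one language group could go unnoticed. The comparison is also between self-selected groups, so even a precise estimate would not isolate the effect of the training language.

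**Working it through.** **Inputs from the article.** 24 dyads; language chosen by the parent, split not stated; pre-post effect size 0.8; α = .05 (sidedness not stated; two-sided reproduces the sample size).

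**Assumptions.** Splits of 12/12 (most favourable), 16/8, 18/6 and 20/4; no dropout; a two-sample t comparison of change scores with equal SDs, as a simple stand-in for the mixed model; all differences in units of the SD of change.

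**1. The plan's own figures.** For a paired comparison with the normal approximation:

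- n = ((1.960 + 0.842) / 0.8)² = 12.26, rounded up to 13, as stated.
- Power at 24 = Φ(0.8 × √24 − 1.960) = Φ(1.959) = 97.5%, against the stated 97%. The noncentral t gives 96.3%.

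This also shows that 0.8 is in SD-of-change units, so a language gap can be put on the same scale.

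**2. Precision of the language contrast.** SE = √(1/n₁ + 1/n₂), df = 22.

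- 12/12: SE = √(1/12 + 1/12) = 0.408; 95% half-width = 2.074 × 0.408 = 0.85.
- 16/8: SE = √(1/16 + 1/8) = 0.433; 95% half-width = 2.074 × 0.433 = 0.90.

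**3. Power of the difference test for one outcome.** Noncentral t with noncentrality d / SE. For 12/12 this is 0.5 / 0.408 = 1.22 and 0.8 / 0.408 = 1.96.

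| Split | Power at 0.5 SD | Power at 0.8 SD | Difference detectable with 80% power | 95% half-width |
|---|---|---|---|---|
| 12/12 | 22% | 47% | 1.20 SD | 0.85 SD |
| 16/8 | 20% | 42% | 1.27 SD | 0.90 SD |
| 18/6 | 17% | 37% | 1.38 SD | 0.98 SD |
| 20/4 | 14% | 29% | 1.61 SD | 1.14 SD |

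For a single outcome, a language gap as large as the whole effect the trial is sized on would be missed 53% of the time at 12/12 (1 − 0.466) and 58% at 16/8 (1 − 0.424).

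**4. What an equivalence test could show.** Two one-sided tests at 5% each, true difference zero, 400,000 simulated draws. The article gives no margin, so a range is shown.

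| Split | Margin 0.5 SD | 0.8 SD | 1.0 SD | 1.25 SD |
|---|---|---|---|---|
| 12/12 | 0.2% | 22% | 53% | 81% |
| 16/8 | 0.1% | 15% | 45% | 75% |
| 18/6 | <0.1% | 8% | 32% | 65% |

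The approximate number per group for 80% power is 2 × ((1.645 + 1.282) / margin)²: about 69 at a 0.5 SD margin and 27 at 0.8 SD.

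**5. Comparability of the groups.** Language is the parent's choice. The planned covariates (services, recruitment site, selected demographics) address part of the imbalance. Demographics enter only if significantly related to the outcome, a screen that itself has little power in 24 dyads. Recruitment and Consent Procedures also assigns a different assessor to each language at screening, and that assessor continues into baseline. The listed covariates do not remove that link.

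**The case against.** The strongest reply is that the article contains no rule turning a non-significant result into equivalence. That is correct. It never mentions equivalence, and it also frames the aim neutrally, as assessing whether language has an impact. A reader might infer that p > .05 is to be declared proof of equal effect, but the documents do not say so. What remains is that a no-difference prediction is stated and no analysis is named that could support it.

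Second, the 53% to 58% miss rate applies to one outcome under an assumed split. It is not the chance that the trial as a whole reports no language difference. Three primary outcomes are measured over time: social communication, parent fidelity and child development knowledge. If a 0.8 SD gap held on all three, the chance that all three tests are non-significant would run from about 15% (0.534³, independent outcomes, 12/12) or 19% (0.576³, 16/8) up to 53% to 58% with perfect correlation. This reply stands, and the figure should be quoted per outcome only.

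Third, the plan does adjust for services, recruitment site and some demographics, and it makes no causal claim about language. This stands too: the fair statement is that residual confounding remains, not that confounding was ignored.

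Fourth, three timepoints and covariates may alter precision. They may do so somewhat, but the shortfall is too large for this plausibly to close it.

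Finally, language is a subsidiary question in a single-group pilot, and the power statement does not extend to it. That limits the weight of the point but does not remove the mismatch.

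**Conclusion.** The point holds as a mismatch between a stated hypothesis and a stated test. It is wrong as written and should be fixed. It does not threaten the trial's main purpose: the pre-post analyses and their sample size are unaffected.

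The sample cannot support a no-difference conclusion at any margin well below the detectable range computed above. Even at 12/12, an interval around an observed difference of zero would reach about 0.85 SD in each direction, wider than the 0.8 effect the trial is sized on. These figures rest on an assumed split, complete data and a simple change-score comparison. Imbalance or dropout would make them worse.

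A reader might also infer that a claim of equal effect would be carried into the planned randomized trial application or the public release. The article says only that pilot results in general will be used for the application. It does not tie release to the language comparison, and its rule for keeping or refining the modules uses satisfaction ratings.

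**What to change.** In Objectives and Study Design, replace the no-difference prediction with an exploratory estimation aim for language.

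In Quantitative Analysis:

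- Report the Spanish-minus-English difference in change from baseline, with its 95% confidence interval, for each primary outcome measured over time.
- State that a non-significant language-by-time term will not be interpreted as no difference or as equivalence.
- Describe the contrast as descriptive, because language is self-selected.

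If a formal equivalence claim is wanted, it belongs in the later, larger trial with a margin fixed in advance.

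The cost is a few sentences of wording. No extra families, visits or measures are needed. The investigators give up a claim that 24 dyads could not have supported.

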### Enrollment and Participation

Over 1 year, 24 parent/child dyads will participate in the study. The parents will receive 6 weekly emails or text messages, each with an active link to access an online training module. All electronic data will be stored in a password-protected university server, and only IRB-authorized personnel will be granted password access.

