### Qualitative Analysis

Focus groups comprised of a subsample of Spanish-speaking and English-speaking parents who have completed the HOLA intervention and follow-up activities will be gathered either on campus or by Zoom. The focus groups will last between 1 and 2 hours, and topics related to intervention satisfaction, alignment with cultural beliefs, and socially valid outcomes will be discussed using a flexible protocol that includes open-ended questions and follow-up probes. The facilitator (bilingual graduate research assistant/PI) will engage all participants and allow additional topics to emerge as necessary, while being sure to discuss all protocol questions. The focus groups will be audio-recorded and transcribed verbatim. Analysis will proceed in 3 stages following a modified grounded theory procedure [34]. Initial codes will be written in the margins, actively summarizing but remaining close to the original text. Next, focused coding will proceed where the most frequent and significant codes will be used to synthesize and organize the data. Finally, codes will be sorted into theoretical categories, and relationships among codes and theoretical categories will be hypothesized [34]. Data from focus groups will inform HOLA intervention improvements and may identify areas of participant growth not measured by quantitative assessments.

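### Parents choose the language and only a total of 24 is targeted, so one version of the training may be estimated very imprecisely; the Spanish-English test is weak at any split

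*Protocol article*

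**What the plan says.** Language is self-selected. The abstract's Objective offers "a series of 6 online learning modules in their choice of Spanish or English", and Recruitment and Consent Procedures sends the weekly links in the parent's preferred language.

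The target is a total. Objectives and Study Design says "we will recruit 24 Latinx toddler-parent dyads (16-36 months old) with elevated risk for ASD", and Enrollment and Participation says "Over 1 year, 24 parent/child dyads will participate in the study". Neither section, nor Recruitment and Consent Procedures, gives an expected split, a target or a minimum by language.

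Several planned uses nonetheless depend on both versions having enough families:

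- an aim: "because participants will choose whether they would prefer to receive the intervention in Spanish or English, we will assess whether language has an impact", both on effectiveness and on satisfaction (Objectives and Study Design);
- a hypothesis: "we predict that there will be no difference in participant outcomes between Spanish and English language trainings" (same section);
- a test: mixed models will "test if changes from baseline on outcome variables differ by parent language preference for training (Spanish or English) over time" (Quantitative Analysis);
- qualitative work: "Focus groups comprised of a subsample of Spanish-speaking and English-speaking parents" (Qualitative Analysis), with low-rated satisfaction items also taken to Spanish and English groups (Quantitative Analysis).

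The one sample-size calculation, in Sample Size Determination, covers the pooled change from baseline to postintervention.

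**The concern.** The stated reason for the study is that brief online training of this kind has not been tested in a bilingual Latinx sample. The recruitment target is satisfied by 24 dyads whether they divide 12/12 or 20/4. In the second case the pooled pre-post result rests almost wholly on one version, and little can be said about change or satisfaction in the other. A pooled satisfaction average could also clear the 3.5 cut-off while the less-used version is rated poorly.

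The number in each language is settled during recruitment. No later analysis can recover families who were not enrolled, so any steer has to be in place before enrolment is complete.

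**Working it through.** **Inputs from the article.** Total of 24 dyads; effect size 0.8; α of .05 (taken as two-sided); stated requirement of 13 for 80% power; stated 97% power at 24.

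**Assumptions.** All 24 complete. Change scores have a common SD, and results are in units of that SD. The splits and preference rates are assumed, because the article gives none.

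**1. The plan's own figure.** For a single-group change, the normal approximation gives n = ((1.960 + 0.842)/0.8)² = 12.26, so 13. Power at 24 is Φ(0.8 × √24 − 1.960) = 97.5%; the paired t test gives 96.3%. The stated figures reproduce, but for the pooled change only.

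**2. Precision by split.** For groups of a and b families:

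- half-width for the language difference = t(.975, 22) × √(1/a + 1/b), with t = 2.074;
- power for the difference from the noncentral t, 22 df, noncentrality 0.8/√(1/a + 1/b);
- half-width for mean change in the smaller group of b families = t(.975, b − 1)/√b;
- power for a pre-post change of 0.8 SD in that group from the noncentral t, b − 1 df, noncentrality 0.8 × √b.

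| Split | √(1/a + 1/b) | Half-width, difference | Power, difference of 0.8 | Half-width, smaller group | Power, smaller group's change of 0.8 |
|---|---|---|---|---|---|
| 12/12 | 0.408 | 0.85 | 47% | 0.64 | 71% |
| 14/10 | 0.414 | 0.86 | 46% | 0.72 | 62% |
| 18/6 | 0.471 | 0.98 | 37% | 1.05 | 36% |
| 20/4 | 0.548 | 1.14 | 29% | 1.59 | 21% |

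Worked examples: with 4 families, 3.182/√4 = 1.59; with 10, 2.262/√10 = 0.72. The within-version half-width for mean satisfaction follows the same formula, in units of the SD of the ratings.

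At 12/12 the smallest language difference detectable with 80% power is 1.20 SD. Detecting 0.8 SD with 80% power would take 25 (normal) to 26 (t) families per language, so 50 to 52 in total.

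**3. How likely a small group is.** The number choosing one language is taken as Binomial(24, p), and either language may be the smaller.

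| Assumed preference | Smaller group 7 or fewer | Smaller group 4 or fewer |
|---|---|---|
| 50:50 | 6% | 0.2% |
| 60:40 | 19% | 1.3% |
| 70:30 | 56% | 11% |
| 75:25 | 77% | 25% |
| 80:20 | 91% | 46% |

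**4. What balance buys.** Going from 4 to 10 families in the smaller group cuts that version's half-width from 1.59 to 0.72 SD, less than half. Going from 18/6 to 14/10 raises power for the language difference only from 37% to 46%. The gain is mainly in the version-specific estimates.

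**The case against.** A reader might infer that the missing minimum is what disables the language comparison, and that a quota would restore it. The figures do not support that. The comparison has 47% power at best, because 24 was sized for the pooled change. Self-chosen language is also confounded with family characteristics, which balance does not cure.

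A reader might also infer that enrolment stops at 24 under a fixed rule, that a small language group could not be assessed for satisfaction at all, or that its focus group would fail. The article writes no closing rule. Its satisfaction cut-off is not defined per language, and a small group can still be described. The focus groups are a subsample with no stated size. These stronger consequences fall away.

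The likelihood of a skewed split is an assumption, and under even preference a very small group is rare. This is also a single-group pilot in which free choice of language serves access, and an article may leave recruitment detail to a fuller document.

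A hard quota has costs of its own. Holding places would make some families wait in a programme meant to reduce the effect of delay, with an upper age limit of 36 months. A strict cut-off at 10 would be arbitrary: 10/14 gives 46% power and 9/15 gives 44%. Even at 50:50 preference the smaller group falls below 10 in about 31% of trials.

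What remains is that the article states its aims by language and its target only in total. The precision available for each version is therefore left to chance, and this can be improved cheaply.

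**Conclusion.** The concern holds in limited form. Nothing in the article steers the language mix, although its aim, its test and its focus groups all draw on both versions. If the split is uneven, one version's change and satisfaction will be estimated very imprecisely: a half-width of 1.05 SD with 6 families or 1.59 SD with 4, against 0.72 SD with 10. How likely this is depends on an unstated preference rate; a group of 7 or fewer has probability about 6% at 50:50, 19% at 60:40 and 56% at 70:30. Any dropout would make the smaller group smaller still.

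The documents do not support the stronger claim that enough families per language would make the comparison informative. The test is weak at every split (47%, 37% and 29% power at 12/12, 18/6 and 20/4), and a non-significant result could not establish the predicted absence of a difference. Balance chiefly protects the version-specific estimates and the focus groups. This is a worthwhile, low-cost improvement, not a flaw that invalidates the pilot.

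**What to change.** 1. Record preferred language at the first telephone call described in Recruitment and Consent Procedures.
2. Set a soft target of about 10 families per language within the 24. Direct the targeted outreach already planned in that section towards the language that lags. Do not hold places or make eligible families wait.
3. Whatever the split, report each version's change and satisfaction with its own estimate and 95% CI.
4. Give the Spanish-English difference as an exploratory estimate with its 95% CI, and state that a non-significant result will not be read as no difference.
5. Report the language preference of all callers.

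The cost is one question at the call, a sentence in the recruitment section and a sentence in the analysis section; the total sample is unchanged. The downside is that some outreach effort is redirected and the enrolled mix may differ from the natural one. Item 5 keeps that difference visible.
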